## Abstract

**Supplementary Information:**

The online version contains supplementary material available at https://doi.org/10.1007/s11357-026-02337-1.

## Introduction

### Background and rationale

Dementia currently affects over 55 million people globally, with projections rising to 139 million by 2050 [1]. Alzheimer’s disease (AD), the most common form of dementia, composes 60–80% of all dementia cases globally [2]. As no curative treatments exist to date, research has increasingly focused on modifiable lifestyle-based strategies that may delay or prevent the onset of mild cognitive impairment (MCI), a prodromal stage of AD. Two such promising modifiable lifestyle-based strategies include sleep and exercise. High-quality sleep, particularly adequate slow-wave sleep (SWS) and rapid eye movement (REM) sleep, has been associated with improved cognition in older adults, especially those with cognitive deficits [3, 4]. Similarly, exercise has been shown to improve cognitive function and preserve hippocampal volume, a decrease of which serves as a prodromal neurobiomarker of AD risk, although the precise biological mechanistic underpinnings to elucidate this remain under investigation [5, 6].

Disrupted sleep has emerged as both a symptom of and contributor to premature neurodegeneration. Short (≤ 6 hours) and long (≥ 10 hours) sleep durations, prolonged sleep latency, and reduced REM sleep have been linked to higher AD risk [7, 8]. These disturbances may act through pathways such as neuroinflammation, insulin resistance, melatonin dysregulation, and/or compromised blood–brain barrier integrity, which, in turn, accelerate cognitive decline [9–11]. Exercise appears to reduce neurodegeneration risk directly through neurogenesis and anti-inflammatory effects [12, 13] as well as indirectly through promoting improvements in sleep quality [14, 15]. Yet, few studies have disentangled the independent versus synergistic effects of sleep and exercise on cognition, AD-linked neuropathology, and cardiometabolic health in older adults who are at higher risk for AD.

Traditionally, neuropsychological testing often required clinical settings, which resulted in limited reachability and scalability. While recent advances in digital health technologies have resulted in the development of multiple remote, application-based cognitive assessments, there is an ongoing need for approaches that optimize the capturing of ecologically valid, real-world cognitive functioning, including cognitive function as it unfolds in naturalistic, dynamic, and contextually meaningful environments. This study will address this need by leveraging the Digital Neuro-Signature Platform, an augmented reality-based cognitive tool that simulates real-world tasks to assess global cognition as well as domain-specific cognitive function, such as learning and memory, executive function, and visuospatial skills [16, 17]. The Digital Neuro-Signature Platform is a novel contribution that builds upon the strengths of existing digital assessments by integrating immersive, behaviorally rich, and context-sensitive paradigms that may enhance sensitivity to subtle cognitive and functional changes that are relevant to AD prevention research. By pairing this with wearable technologies, including the Elemind Neuromodulation headband, Fitbit, and Lys light sensor, behavioral and physiological data on sleep and exercise will be unobtrusively captured while simultaneously improving assessment fidelity and participant engagement.

This pilot trial is designed to address critical scientific, clinical, and public health gaps by generating preliminary evidence at the intersection of sleep, exercise, and cognitive aging. Scientifically, the study will provide early-stage data on how two non-pharmaceutical, lifestyle-based health behaviors—sleep and physical activity—independently and jointly relate to cognitive performance, AD-linked neuropathology, and cardiometabolic risk in older adults with and without MCI. Clinically, the trial will evaluate the feasibility and signal of a novel, technology-enabled, scalable intervention across varying levels of cognitive risk, yielding effect size estimates and mechanistic insights to inform the design of larger, fully powered trials. Collectively, these findings will lay the groundwork for future personalized behavioral interventions and early-detection platforms that can be integrated into routine clinical and community-based care settings.

### Objectives

The main objectives of this exploratory, hypothesis-generating trial are to (1) assess whether improvements in sleep architecture (e.g., SWS, REM sleep), total sleep time, and sleep quality (e.g., increased sleep efficiency, decreased sleep onset latency and restlessness [restless bouts/hour]) are associated with improved cognitive performance and biomarker panels for brain and cardiometabolic health; (2) evaluate the effects of structured, moderate-level aerobic and anaerobic exercise on cognitive performance and biomarker panels for brain and cardiometabolic health; (3) examine the combined, potentially synergistic effects of the sleep and exercise interventions on cognitive performance and biomarker panels for brain and cardiometabolic health; and (4) investigate the role of light exposure as a potential modulator of sleep parameters.

The central hypotheses of this trial are that (1) disrupted baseline sleep architecture, short and long durations, and lower sleep quality measures as well as less physical activity will be linked with poorer cognition and more adverse brain and cardiometabolic biomarker profiles at baseline; (2) improvements in sleep metrics (i.e., increased sleep efficiency, SWS, REM, and total sleep time, as well as reduced onset latency and restlessness) will independently correspond to cognitive improvements and favorable biomarker changes during the 8-week intervention; (3) increased exercise will be independently associated with better cognitive, brain, and cardiometabolic health; (4) the combined sleep and exercise group will demonstrate greater improvements in cognitive function and biomarker profiles for brain and cardiometabolic health; and (5) these changes will be more pronounced in individuals with MCI compared to age- and sex-matched, cognitively normal (CN) controls. Given the short trial duration, this trial is explicitly intended for signal detection, building on similar 8-week studies of lifestyle-based behavioral interventions that have successfully detected early cognitive and physiological response patterns.

## Methods

### Study design overview

*Combating Alzheimer’s through Sleep and Exercise (CASE)* is a single-center, three-arm, randomized trial that will investigate the effects of sleep, exercise, and a combination of these on cognitive function as well as brain and cardiometabolic biomarker outcomes in older adults with and without MCI. Participants will be randomly assigned via Research Electronic Data Capture (REDCap [18, 19]) to one of three groups: (1) exercise-only, (2) sleep-only, or (3) combined sleep and exercise. Each group will receive the following intervention-specific digital tools: (1) all groups will receive a Fitbit to continuously track physical activity, including the tracking of all in-person, biweekly, 60-minute exercise interventions; (2) the sleep-only and sleep + exercise groups will receive the Elemind Neuromodulation headband for personalized acoustic stimulation; and (3) the sleep-only and sleep + exercise groups will receive a Lys device for monitoring light exposure.

The intervention will span 8 weeks and will follow structured phases, including screening, baseline assessment, intervention, and follow-up. Full Digital Neuro-Signature Platform augmented reality cognitive assessments will be used to assess cognition at baseline and week 8 (post-intervention) as well as biweekly as brief pulse assessments throughout the trial duration. Blood-based biomarkers will be collected via venipuncture at Quest Diagnostics at baseline and post-intervention under standardized fasting conditions. Specifically, in order to maximize participant safety and minimize any potential influences of acute exercise [20], the pre-intervention blood draws will be obtained no sooner than 24 hours and no later than seven (7) days before the initiation of the first exercise session, and post-intervention blood draws will be obtained within 24–48 hours after completion of the final exercise session. No blood draws will occur on the same day as in-lab exercise. Data from digital devices will be temporally synchronized using structured protocols to support integrated analysis, and raw sleep data will be reviewed for artifacts, with re-instruction provided for invalid nights. Patient-Reported Outcomes Measurement Information System (PROMIS) surveys [21] and validated physical activity questionnaires (including the Physical Activity Scale for the Elderly (PASE [22]) and the Community Healthy Activities Model Program for Seniors (CHAMPS [23])) will be administered via REDCap at baseline (week 0) and at week 8 during the in-person visits. The CASE study is designed to assess adherence, detect early efficacy signals, and explore behavioral mechanisms that may prevent or delay AD through modifiable lifestyle-based behavior interventions.

### Study procedures

#### Participants

Eligible participants must meet all of the following: (1) 55–80 years of age, reflecting growing evidence that individuals may experience increased AD risk starting in midlife [24, 25]; (2) able to safely perform moderate-intensity exercise as per the Physical Activity Readiness Questionnaire (PAR-Q, a validated exercise readiness questionnaire [26]); (3) able to wear and use Fitbit wristwatch and/or the Elemind Neuromodulation headband and Lys devices; (4) able to operate a digital device, such as mobile phone or computer; (5) able and willing to provide venous blood samples; (6) able to understand and speak English fluently (currently, there remains a lack of validated, multilingual versions of the Digital Neuro-Signature Platform and associated study interfaces; presently, such validated tools are only available in English, and the utilization of non-validated translations may introduce measurement bias, particularly regarding cognitive outcomes); (7) able to self-report a history of cognitive changes or impairment; and (8) be cognitively able (including those with MCI) and willing to provide informed consent.

Prospective participants will be excluded in the case of (1) severe mobility limitation(s) that prevent(s) safe participation in moderate exercise protocols; (2) unstable or uncontrolled medical conditions (e.g., recent cardiovascular event (≤ 6 months), cerebrovascular accident or transient ischemic attack (≤ 6 months), active cancer, or uncontrolled diabetes) that pose safety concerns; (3) inability to complete intake screening procedures; (4) severe uncorrected hearing impairment, particularly if it precludes effective utilization of the Elemind Neuromodulation headband, and/or vision impairment that interferes with digital device usage or in-person exercise guidance; (5) determined to have Alzheimer’s/dementia based on performance on the Quick Mild Cognitive Impairment (QMCI [27]; see Table 1); (6) inability or unwillingness to learn or engage with digital devices (e.g., smartphone, Fitbit, Elemind, or Lys), even with staff support; (7) regular pre-study engagement in ≥ 150 minutes of moderate-level and/or ≥ 75 minutes of vigorous-level exercise per week based on Fitbit data obtained during the initial 7-day onboarding screening period; (8) determined to have adequate sleep metrics, including duration (mean 7–9 hours) and quality (sleep efficiency ≥ 80% [28]), pre-intervention based on Elemind Neuromodulation headband data obtained during the initial 7-day onboarding screening period; and (9) current usage of disease-modifying therapy targeting amyloid (e.g., anti-amyloid monoclonal antibodies) or tau.

**Table 1 Tab1:** Quick Mild Cognitive Impairment score thresholds by cognitive status

	**Aged ≤ 75, education < 12 years**	**Aged ≤ 75, education ≥ 12 years**	**Aged > 75, education < 12 years**	**Aged > 75, education ≥ 12 years**
CN	≥ 66	≥ 70	≥ 64	≥ 64
MCI	55–65	58–69	51–63	52–63
Dementia	< 55	< 58	< 50	< 51

Table describes the score thresholds of the Quick Mild Cognitive Impairment screening tool to suggest cognitive status (i.e., cognitively normal, mild cognitive impairment, or dementia) based on adjustments for dichotomized age and educational attainment. Higher scores indicate better cognitive function. *CN*, cognitively normal; *MCI*, mild cognitive impairment; *QMCI*, Quick Mild Cognitive Impairment screen

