#### Screening and consent

A trained research assistant will conduct a brief phone pre-screening with all interested prospective participants. During this call, the research assistant will collect key demographic information (e.g., age, sex, education level, and smartphone ownership) and administer two validated screening tools: the Quick Mild Cognitive Impairment screen (QMCI, a clinician-administered tool used to assess objective cognitive status [27]) and the Physical Activity Readiness Questionnaire (PAR-Q, which evaluates the participant’s ability to safely engage in moderate exercise [26]; (see Table 2)). Both assessments will require fewer than five minutes to complete. Participants must achieve a QMCI score at or above the specified age- and education-adjusted scoring thresholds that indicate either CN or MCI status (see Table 1 [29, 30]) and report no contraindications to performing moderate-intensity exercise on the PAR-Q. Subjects who score below these thresholds will be excluded from the trial; no borderline adjudication process will be applied to ensure clarity and reproducibility.

**Table 2 Tab2:** Screening questionnaires

Questionnaire	Description and variables collected
Basic Info Screening Form (eligibility criteria)	Age, whether prospective subjects own and can operate a smartphone/computer device
Physical Activity Readiness Questionnaire (PAR-Q)	Safe for participants to perform moderate-level exercise. This will be the main factor in determining if it is safe to perform the moderate-intensity exercise routine for participants; an emergency plan is detailed later in the study
Quick Mild Cognitive Impairment screen (QMCI) 6-item	A clinician-administered tool used to assess objective cognitive status

Table describes the screening questionnaires that will be to evaluate the eligibility of each prospective participant as well as a descriptive identification of which variables of particular interest will be collected

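### In Table 1 the dementia and MCI bounds do not meet in the two over-75 columns, so one bound in each column appears to be off by one point

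*Protocol article*

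**What the plan says.** Table 1, in the Participants section, sorts QMCI scores into three categories within four columns: age 75 or younger with under 12 years of education, age 75 or younger with 12 or more, over 75 with under 12, and over 75 with 12 or more. In that column order its rows read:

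- "CN ≥ 66 ≥ 70 ≥ 64 ≥ 64"
- "MCI 55–65 58–69 51–63 52–63"
- "Dementia < 55 < 58 < 50 < 51"

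Two rules use the table. Exclusion criterion 5 removes anyone judged to have dementia "based on performance on the Quick Mild Cognitive Impairment (QMCI [27]; see Table 1". The Screening and consent section sets a positive requirement: "Participants must achieve a QMCI score at or above the specified age- and education-adjusted scoring thresholds that indicate either CN or MCI status". It then adds: "Subjects who score below these thresholds will be excluded from the trial; no borderline adjudication process will be applied to ensure clarity and reproducibility".

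The age range for entry is "55–80 years of age", so the two over-75 columns will be used. Under Participant recruitment, the CN/MCI distinction is also the stratification factor for randomisation, with about 30 participants planned in each category.

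**The concern.** A cut-off table that decides entry should place every possible score in exactly one category. In the two younger columns it does. In the two older columns one score falls between the top of the dementia row and the bottom of the MCI row.

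Criterion 5 works from the dementia bound and the entry requirement works from the MCI lower bound. In the younger columns these are the same number, so the two rules coincide. In the older columns they differ by one point, which suggests that one of the two printed figures is wrong.

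What is at stake is the entry threshold for people aged 76 to 80. If the MCI lower bound is the wrong figure, the trial screens out at the telephone stage a few people whom it intended to recruit as MCI. If the dementia bound is wrong, nobody's eligibility changes and only the recorded reason for screen failure is affected. Because borderline adjudication is ruled out, nobody reviews these scores case by case, and the printed figure decides.

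**Working it through.** The plan states no derived figure to reproduce here. The check is whether the table is complete and whether the two rules use the same bound.

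**Inputs.** All come from Table 1. Let D be the dementia cut-off (dementia if the score is below D), L and U the lower and upper ends of the MCI range, and C the CN cut-off (CN if the score is C or more). Scores are taken as integers, as the printed ranges imply.

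**Formulas.**
- Unclassified integers between dementia and MCI: L − D, namely the scores s with D ≤ s < L.
- Unclassified integers between MCI and CN: C − (U + 1).
- A positive result is a gap, zero means the rows meet, and a negative result is an overlap.

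| Column | D | L–U | C | L − D | C − (U + 1) | Unclassified |
|---|---|---|---|---|---|---|
| ≤ 75, < 12 years | 55 | 55–65 | 66 | 55 − 55 = 0 | 66 − 66 = 0 | none |
| ≤ 75, ≥ 12 years | 58 | 58–69 | 70 | 58 − 58 = 0 | 70 − 70 = 0 | none |
| > 75, < 12 years | 50 | 51–63 | 64 | 51 − 50 = 1 | 64 − 64 = 0 | 50 |
| > 75, ≥ 12 years | 51 | 52–63 | 64 | 52 − 51 = 1 | 64 − 64 = 0 | 51 |

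Classifying every integer from 0 to 100 in each column gives the same result: two unclassified scores and no overlaps.

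**The two rules at those scores.** Criterion 5 excludes when s < D. The entry requirement excludes when s < L.

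- Over 75, under 12 years, s = 50: 50 < 50 is false, so criterion 5 does not apply. 50 < 51 is true, so the entry requirement excludes.
- Over 75, 12 or more years, s = 51: 51 < 51 is false, so criterion 5 does not apply. 51 < 52 is true, so the entry requirement excludes.

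At every other integer in all four columns the two rules agree.

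**What each correction would do.** In each over-75 column the rows can be made to meet by moving one of two cells:

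- If the dementia cut-off rises by one (50 to 51; 51 to 52), the unclassified score becomes dementia. Eligibility is unchanged, and criterion 5 now gives the reason for exclusion.
- If the MCI lower bound falls by one (51 to 50; 52 to 51), the unclassified score becomes MCI. A person who is now excluded would pass the QMCI requirement.

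The document gives no basis for choosing between them.

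**The case against.** The strongest reply is that eligibility criteria apply together. Not meeting criterion 5 does not make a person eligible; it means only that this ground for exclusion is silent. The Screening and consent section then decides, and it relies only on the MCI lower bound, which is printed in all four columns. Every integer score therefore gives a single enter-or-exclude answer.

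That reply stands, and it rules out three stronger readings that a reader might infer from the gap:

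- That the two rules give opposite answers. They differ only if each is read alone. Read jointly, a 50 or 51 is excluded.
- That the table cannot be applied reproducibly for entry. It can, because the entry threshold is explicit, and the refusal to adjudicate makes the result more fixed.
- That some randomised participants would have no stratum. The strata are CN and MCI, and that boundary is contiguous in every column. The gap lies below the entry threshold, so nobody in it is randomised under the rules as written.

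The reply does not show that the MCI lower bound is the intended figure. Reading the rules together yields an answer by taking that bound as printed, and the mismatch with the dementia row is what puts it in doubt. It also leaves people excluded on a cognitive score to which the table gives no label.

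**Conclusion.** The inconsistency is real and minor. Table 1 leaves a score of 50 (over 75, under 12 years of education) and a score of 51 (over 75, 12 or more years) in no category. Under the rules as written both are excluded. The open question is whether they should be: if the MCI lower bound is the misprinted figure, the entry rule turns away people whom the table was meant to classify as MCI.

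The reach is one integer score in each of two columns, at ages 76 to 80. The document gives no score distribution, so the number of people affected cannot be estimated; it may well be none. No power figure, endpoint, randomisation stratum or analysis model depends on the answer.

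The conclusion rests on two assumptions. One is that QMCI scores are integers. The other is that the three categories were meant to cover the whole scale, as they do in both younger columns. All twelve cells of the table are present and legible, and the same one-point gap appears in both older columns, so damage in text extraction is an unlikely explanation.

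**What to change.** Check the over-75 MCI and dementia cells of Table 1 against the cut-off sources cited in Screening and consent, and correct whichever is wrong so that the rows meet, as they do in the younger columns. Then state criterion 5 and the entry threshold as the same bound, for example by having both refer to the lower end of the MCI range.

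The cost is one corrected cell in each of two columns and a short wording change. Sample size, randomisation and analysis are untouched. If the MCI bound is the one that moves and screening has already started, the telephone pre-screening log should be checked for people aged 76 to 80 who were turned away at exactly 50 or 51 in the relevant column.

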#### Participant recruitment

A total of 60 participants comprised of approximately 30 CN older adults and 30 older adults with MCI will be enrolled in this study. Recruitment strategies will consist of a combination of the following:Participants will be recruited from existing studies and research registries maintained by the Translational Sleep and Circadian Sciences (TSCS) Laboratory at the University of Miami Miller School of Medicine. All individuals considered for enrollment will have previously consented to be contacted for future research opportunities. Initial contact will be made via phone by trained study personnel to confirm interest and screen for eligibility.In addition, recruitment will include referrals for prospective participants with an MCI diagnosis from the Division of Cognitive Neurology at the University of Miami.Moreover, flyers and social media advertisements will be distributed throughout southern Florida to further aid in recruitment efforts.This trial will participate in the University of Miami’s Consent to Contact program, which allows approved researchers to access a database of University of Miami Health System patients who have agreed to be contacted about participating in clinical research studies.

Recruitment and enrollment procedures will comply with all institutional and federal guidelines, including the Health Insurance Portability and Accountability Act (HIPAA), to ensure privacy and confidentiality of all protected health information that is obtained. Eligible participants will be equally randomized (*n* = 20 per group) into three study arms: sleep-only, exercise-only, or combined sleep and exercise. Stratified randomization by cognitive status will be employed to ensure balanced representation across groups (i.e., each group will be comprised of 10 CN participants and 10 participants with MCI).

